### Interim analyses {21b}

There are no interim analyses planned for this study.

### Methods for additional analyses (e.g., subgroup analyses) {20b}

In addition to our primary analyses, we plan to analyze the results of participants who completed the intervention per protocol, in that they attended all the coaching or health education sessions. We will also conduct exploratory analyses based on clinically significant improvements in sleep and analyze the results among participants in the intervention group that extended their sleep duration by at least 30 min and for those who met criteria at 8 weeks of having sleep duration over 7 h. Finally, we plan to test the impact of obstructive sleep apnea as a moderator of sleep and cardiometabolic outcomes. We will conduct moderator analyses of participants to test the results of the intervention among participants with mild obstructive sleep apnea (5–15 apneas per hour at screening) compared to those with < 5 events per hour.

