**Fig. 2 Fig2:**
[figure not shown]
Schedule of time points, study assessments, and interventions

After web or telephone screening, participants will complete a baseline/screening visit. Participants will undergo standardized BP screening to determine BP eligibility. The BP screening protocol involves 3 unattended BP recordings taken with an automated BP machine (HEM-907HL, OMRON Healthcare Inc.) after a 5-m quiet resting period and 3 m between measurements. If they meet the study criteria, they will review the consent form with the study staff and complete the informed consent prior to continuing the study visit. Participants will complete self-reported questionnaires and cognitive testing and then will wear the study devices at home over the next 10 days (Apnea link monitor for 1 night, ambulatory blood pressure monitor (OnTrak Ambulatory Blood Pressure Monitor 90,227, Spacelabs Inc.) for 24 h, and actigraphy and physical activity monitor for 10 nights). At the end of the baseline period, participants will return to the lab to download their devices and will have their blood drawn. If eligible for the study, they will be randomized to either the sleep extension intervention group or the education control group. They will receive a study letter and materials in the mail, as well as a call from the study coach informing them of their group assignment. The study interventions have 3 main periods. In the intervention period (study weeks 1–8), participants will receive 8-weekly intervention or control sessions and content. In the maintenance period (months 2–6), participants will receive monthly intervention or control sessions and materials. Finally, in months 6–12, participants will be observed, but there will be no interventions delivered.

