### Sample size {14}

Our power calculations are based on the assumption that the standard deviation (SD) for change in sleep duration from baseline to 8 weeks will not exceed 37.4 min, which is 10% higher than the SD for change in sleep duration of 34 min reported after 40 days in our previous study [22]. We also assume the Pearson correlation between baseline and follow-up sleep duration will not exceed 0.75, and that the attrition rate will not exceed 20%. Under these assumptions, 120 randomized participants (60 in each of the treatment and control groups) will provide at least 80% power with 2-sided *α* = 0.05 to detect a treatment effect of 20.2 min.

If we also assume that (1) the SD for baseline SBP will be $$\le$$ 11.8 mmHg, which is 10% higher than the average baseline SD reported in two previous studies [refs]; (2) the Pearson correlation between the baseline and 8-week follow-up SBP values will be $$\ge$$ 0.70; and (3) the attrition will be $$\le$$ 20%, and the sample size of 60 patients per treatment group will additionally ensure at least 80% power for the main secondary analysis to detect a treatment effect on the change in SBP of 4.86 mmHg.

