### Data collection and management

#### Plans for assessment and collection of outcomes {18a}

##### Screening measures

Participants will complete self-report measures to evaluate for the presence of elevated depressive symptoms and symptoms of common sleep disorders on the web/phone prescreening. Participants who demonstrate elevated depressive symptoms (score ≥ 15) on the PHQ-8, moderate severity of restless legs (score ≥ 11) on the International Restless Legs Working Group Questionnaire, or severe insomnia on the Insomnia Severity Index [23] and scores ≥ 3 on the STOP questionnaire [24] will be excluded. At the baseline/screening visit (visit 1), participants who are at risk for OSA (STOP = 2) will complete one night with the Apnea Link monitor (Resmed, Inc.) to screen for the presence of obstructive sleep apnea. Participants who have moderate severity or greater OSA (Apnea Hypopnea Index ≥ 15) will be excluded from the study. They will be mailed a notification letter with screening results recommending they discuss the results with their provider.

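### The sleep-apnea moderator test uses only a split of the apnea index at 5 events per hour; a prespecified continuous-index interaction should stand beside it

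*Protocol article*

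**What the plan says.** Protocol article, Methods for additional analyses {20b}, states: "we plan to test the impact of obstructive sleep apnea as a moderator of sleep and cardiometabolic outcomes". It then fixes the contrast: results "among participants with mild obstructive sleep apnea (5–15 apneas per hour at screening) compared to those with < 5 events per hour". No analysis with the index on its numeric scale is mentioned.

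Screening measures (under {18a}) shows where the index comes from. It is the apnea-hypopnea index (AHI) from a one-night home recording, and anyone with "Apnea Hypopnea Index ≥ 15" is excluded. Among randomized participants the index therefore runs from 0 to below 15.

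Two sections differ on who has an index. Screening measures says "participants who are at risk for OSA (STOP = 2) will complete one night with the Apnea Link monitor". The Participant timeline {13} (text under Fig. 2) lists "Apnea link monitor for 1 night" among the baseline devices, with no such restriction.

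Sample size {14} powers only the main effects. It gives no power, AHI distribution or share with mild apnea for the moderator test.

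**The concern.** With the two-group split, a participant at 4.9 events per hour counts as different from one at 5.1 and the same as one at 0. All variation in the moderator within each group is discarded. If the treatment effect changes gradually with apnea severity, the test has less power than the data allow.

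An interaction test in a trial of this size starts weak, so any avoidable loss matters. The practical risk is that a non-significant interaction is taken as evidence that mild apnea does not alter the response to sleep extension, when the test could have detected only a very large difference. The form of the moderator is stated in {20b}, so this is a comment on a stated method and not on detail left to an analysis plan.

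**Working it through.** **Inputs, Sample size {14}.** SD: "change in sleep duration from baseline to 8 weeks will not exceed 37.4 min". Correlation: "the Pearson correlation between baseline and follow-up sleep duration will not exceed 0.75". 120 randomized 1:1 with 20% attrition leaves 96 analysed, 48 per arm. Stated detectable effect: 20.2 min.

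**Step 1. Reproduce the plan's figure.** ANCOVA residual SD = SD of change × √((1 + r)/2) = 37.4 × √0.875 = 34.98 min. With 48 per arm, 80% power and two-sided α = 0.05, the detectable effect is 20.0 min (normal) or 20.2 min (noncentral t, 93 df). The stated figure is reproduced.

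**Step 2. Strength of the split test.** Let p be the share with mild apnea (assumption; not in the document). SE of the interaction = 34.98 × √(2/(48p) + 2/(48(1 − p))). The detectable difference is 2.80 × SE. Power for a 20.2-min difference is Φ(20.2/SE − 1.96).

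| p | SE (min) | Detectable difference (min) | Power for 20.2 min |
|---|---|---|---|
| 0.50 | 14.28 | 40.0 | 29% |
| 0.30 | 15.58 | 43.7 | 25% |
| 0.25 | 16.49 | 46.2 | 23% |
| 0.20 | 17.85 | 50.0 | 20% |

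The detectable interaction is 2.0 to 2.5 times the detectable main effect.

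**Step 3. Information lost by the cut.** If moderation is linear in AHI, the loss is 1 − corr(AHI, indicator of AHI ≥ 5)². All shapes are assumptions.

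- Uniform on 0–15: 33%.
- Exponential truncated at 15, mean 3–10 before truncation: 29–33% (44% at mean 2).
- Log-normal truncated at 15, median 3–6: 30–43%. It reaches 50–52% when the cut lies far from the centre.
- Moderation linear in log AHI: 33–74%.
- Moderation a true step at 5: 0%.

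A loss of one third makes 96 participants count as 96 × 2/3 = 64 for this test.

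**Step 4. What a continuous index recovers.** Under linear moderation, 20.2/SE is divided by √(1 − loss). Take losses of 29% and 36%.

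- p = 0.50: 1.414/√0.71 = 1.68 gives 39%; 1.414/√0.64 = 1.77 gives 42%. The split gives 29%.
- p = 0.30: 1.296/√0.71 = 1.54 gives 34%; 1.296/√0.64 = 1.62 gives 37%. The split gives 25%.
- p = 0.20: 1.131/√0.71 = 1.34 gives 27%; 1.131/√0.64 = 1.41 gives 29%. The split gives 20%.

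**Step 5. Simulation in both directions.** n = 96, residual SD 34.98 min, truncated exponential index with mean 5. The mean index then differs by about 6.3 events/h between the two groups.

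| True moderation | Split | Linear AHI |
|---|---|---|
| 4 min per event/h | 36% | 48% |
| 5 min per event/h | 53% | 68% |
| 6 min per event/h | 68% | 82% |
| Step of 30 min at 5 | 49% | 36% |
| Step of 43 min at 5 | 78% | 64% |

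Slopes of 4, 5 and 6 imply between-group differences of about 25, 32 and 38 min, all above the 20.2-min main effect. At 3.2 min per event/h (3.2 × 6.3 ≈ 20 min) the continuous test gains about 6 to 9 points. At 2 min per event/h it gains 2 to 3. Under the two steps, log(AHI + 1) gives 33% and 57%.

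**Step 6. If fewer people have an index.** With half the sample recorded and an even split, the detectable interaction is about 57 min and power for 20.2 min is about 17%.

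**The case against.** The split has a real defence. The stated question concerns a clinical category, mild apnea, and the cut pairs with the threshold of 15 used for exclusion. It is fixed in advance, is not driven by data, and sits among additional analyses with no claim of power.

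The loss also runs both ways. If the effect steps at 5, a linear model has less power than the split, as Step 5 shows. Most of the weakness comes from having 96 participants, and a continuous model stays far below 80% at any plausible effect. The gains of 12 to 15 points appear only at gradients larger than the effect the trial is sized for. Nothing in {20b} forbids a continuous model as support.

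All of this stands. It rules out two readings that a reader might infer: that a third of the information is certainly lost, and that the cut is the main reason the test is weak. The first needs an AHI distribution and a graded effect, and the documents supply neither. The second is contradicted by Steps 2 and 4. Nor does it follow that the clinical groups should be reduced to description.

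What remains is that the document names only one form of the moderator and gives no argument for a step at 5. A graded effect is at least as natural a possibility, and the plan has no prespecified test suited to it.

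**Conclusion.** The point holds in a limited form. As the only moderator analysis named, the split costs roughly 30–50% of the information in the index if moderation is graded, and nothing if the effect steps at 5. Those figures depend on assumed index shapes and on linearity in AHI.

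The test is weak under either form. For a 20.2-min interaction, power is about 20–29% with the split over mild-apnea shares of 20–50%. With a continuous index and linear moderation it is about 34–42% for shares of 30–50%, and 27–29% at a share of 20%. These figures also assume that all 96 analysed participants have an index. If only those at STOP = 2 are recorded, the moderator is missing by design for lower scores, which could cost more than the split.

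A reader might expect the protocol to treat a null interaction as showing that apnea is irrelevant. It does not say so, and the advice on interpretation below is a precaution. This is an optional improvement to an additional analysis and does not touch the primary result.

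**What to change.** In {20b}:

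- Prespecify an arm by continuous-AHI interaction with one functional form named in advance, either AHI or log(AHI + 1).
- Report the estimated treatment effect with confidence intervals at chosen values, for example 0, 5 and 10 events per hour.
- Keep the comparison of < 5 with 5 to < 15 beside it as the clinically labelled contrast. Writing the upper bound as below 15 matches the exclusion in Screening measures.
- Name the AHI of Screening measures as the index throughout. Section {20b} now moves between apneas and events per hour.
- State that a non-significant interaction will not be read as absence of moderation.

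Reconcile the Participant timeline {13} with Screening measures on who has the index recorded, and define the moderator analysis set accordingly.

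This needs no new data. The costs are one more exploratory model, a functional form that must be fixed beforehand, and lower power than the split for that model if the true effect steps at 5. Keeping both analyses covers that last case.

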### Methods in analysis to handle protocol non-adherence and any statistical methods to handle missing data {20c}

We plan to apply multiple imputation to impute missing outcome data, using comprehensive imputation models that include both non-missing measurements from the variables included in the data analysis as well as additional auxiliary variables that are considered to be predictive either of the risk of missingness or the values of the variables whose missing values are being imputed. The multiple imputation approach has been established as superior to alternatives, including complete case analysis or simplified ad hoc single imputation approaches [39, 40].

### Plans to give access to the full protocol, participant-level data, and statistical code {31c}

De-identified data and a codebook will be provided upon written request to the contact PI ([name]).

### Oversight and monitoring

#### Composition of the coordinating centre and trial steering committee {5d}

This study does not have a coordinating centre or trial steering committee. [name] and [name] (co-PIs) are jointly responsible for the conduct of the study. [name] is the contact PI and is responsible for the day-to-day study operations, overseeing the local study staff who are conducting recruiting and data collection activities and responsible for communications with NIH. [name] is responsible for the coaching component of the study, including overseeing the training of the study coach and conducting fidelity assessments of the intervention and control groups. The executive team will meet monthly and is led by [name] and includes [name] and the co-PIs as well as the project coordinator and staff. The study operations team, including Drs. [name], [name], the biostatistician ([name]), study coordinator, and research assistant, will meet weekly to review the study progress and proactively address any potential issues or slowdowns. The data management team (led by [name]) consists of the University of Utah Biomedical Informatics Core (BMIC), the statistician ([name]), and co-I/senior statistician, [name]. This team provides administration and technical staff to support the development of case report forms in REDCap, as well as automated prompt, reminders, randomization modules, and overseeing blinding in the study database. The recruitment and data collection will be conducted by the study coordinator and research assistant. Their day-to-day activities will be supervised by [name], who is on site at the research office. There is not a formal stakeholder and public involvement group in this trial.

#### Composition of the data monitoring committee, its role, and reporting structure {21a}

Due to the low-risk nature of the study, there is no data monitoring committee. The study team has appointed an independent safety monitor to review any potential adverse events during the study.

#### Adverse event reporting and harms {22}

Given the non-invasive nature of the intervention, no new adverse events are expected. Adverse events will be assessed at each study visit and between visits if reported during the study period. Adverse events will be reported according to the standard procedures. The team will review such events and rate them as *likely*, *possible*, or *unlikely* in relation to study interventions. Any unexpected serious adverse events or unanticipated problems involving risks to participants that are possibly related to the study will be promptly reported to the PI, safety monitor, IRB, and assigned NINR program officer in accordance with relevant rules and regulations. Investigators will submit yearly progress reports to IRB and NINR summarizing data and safety monitoring activities, including adverse events deemed expected or unrelated to the study and protocol.

#### Frequency and plans for auditing trial conduct {23}

The study investigators will submit an annual report to the study sponsor (National Institute of Nursing) including details of enrollment in the past year, progress on the study aims, and any barriers to completing the study. The study progress will be reviewed by NIH via the yearly progress report. The team will also submit a yearly report to the University of Utah Institutional Review Board (IRB). The team will internally audit the study records yearly throughout the trial period.

#### Plans for communicating important protocol amendments to relevant parties (e.g., trial participants, ethical committees) {25}

Plans for protocol modifications will first be approved by the sponsor (NIH). Then, any modifications will be approved by the IRB and updated in ClinicalTrials.gov. Participants will be notified of the protocol changes, if applicable, at their next study visit, where they will complete an updated informed consent form if necessary. Any protocol deviations will be documented in the protocol deviation form and reported to the IRB.

#### Dissemination plans {31a}

The study team will share updates to the participants approximately quarterly and will send a result summary at the end of the study. The results of the study will be presented at international conferences and publications in peer-reviewed journals. The team will work with their institutions and use social media to highlight the presentations and publications from this study.

## Discussion

This study aims to test the effects of a real-world behavioral sleep extension intervention on sleep and cardiometabolic health among adults with elevated BP/stage I/II hypertension and short sleep duration. Despite the effectiveness of other behavioral sleep medicine treatments, such as cognitive behavioral therapy for insomnia (CBT-I) [41], there are limited interventions to extend sleep among individuals with short sleep duration. Therefore, results of this intervention have the potential to translate behavioral sleep interventions to a sleep problem that is common, associated with mental and physical health and currently not served by existing interventions.

The main feature of our intervention is the use of coaching combined with wearable technology to motivate behavior change. In our previous research, the use of consumer sleep technology was rated as highly desirable to individuals with short sleep duration and, in our intervention development, was rated as the most enjoyable aspect of the study [42, 43]. The addition of the coach is a critical aspect of this treatment. Prior research from our laboratory and others suggests that a wearable device alone is not sufficient to change sleep [44]. The coaching protocol is designed based on the principles of supportive accountability, which includes that the coach is knowledgeable and supportive but also someone who will hold the participant accountable for their behavior [45]. As such, the combination of the wearable device and a supportive person who is viewing and discussing the data with the participant has been successful in our pilot studies in motivating behavior change.

An important limitation to note is that this intervention focuses on extending sleep among individuals who are able to extend their sleep opportunity. We acknowledge that the causes of short sleep duration are multifactorial, and only some aspects are modifiable. Particularly relevant to communities of color, longstanding structural barriers affect sleep contributing to disparities cardiometabolic disease risk [46]. Substantial barriers faced by individuals due to work schedules, child care, and time spent using public transportation are all less modifiable than volitional causes of short sleep duration including bedtime procrastination and leisure activities such as watching TV [47].

In summary, the results of this study will demonstrate the short-term (8 weeks) and longer-term (12 months) effects of behavioral sleep extension. Future research is needed to study in other populations, biopsychosocial contributors to individual differences in who can and cannot extend sleep and also to understand interventions geared toward maintenance of behavior change.

## Trial status

Protocol ver 1.0 (date 06/28/23).

Recruitment began: 3/15/2021.

Anticipated recruitment completion date: 1/1/2024.

## Data Availability

De-identified data and a study codebook will be made available at the end of the study upon request to the contact PI (KB).

## Abbreviations

EMR: Electronic medical records
CMD: Cardiometabolic disease
HTN: Hypertension
SBP: Systolic blood pressure
